### Statistical analysis

Statistical analyses of all data will be performed using the SPSS software version 21.0 (SPSS Inc., Chicago, IL, USA). To handle non-adherence, we will use the intention-to-treat approach for data analysis. Missing values will be dealt with using the last observation carried forward (LOCF) method. Data will be expressed as mean ± standard deviations (± SD) and percentages. The one-sample Kolmogorov–Smirnov test will be used for assessing the normality of the distribution of data. In the case of a non-normal distribution of a variable, we will apply the log transformation. If the variables were non-normally distributed even after log transformation, we would use non-parametric tests in the analyses. Continuous variables will be compared between the two groups by independent samples *t*-test (or its non-parametric equivalent). We will apply the chi-square test to examine the distribution of participants in terms of categorical variables. To find the effect of the intervention on outcome variables, repeated measures analysis of variance (or its non-parametric equivalent) will be used. In these analyses, the effect of the intervention, time, and time-intervention interaction will be explored. The potential difference in baseline levels of outcome variables as well as differences in dietary intakes and physical activity levels, if any, between the two groups will be controlled for in these analyses. *P* values will be considered significant if they were < 0.05.

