**Methods:**

This study is a randomized, double-blind clinical trial, in which forty patients with mild to moderate severity of RA will be randomly allocated to receive either 30 g/day probiotic cheese (*n* = 20) or only low-salt and low-fat cheese without any added probiotic (*n* = 20) for 12 weeks. Assessment of anthropometric measures and biochemical indicators, including serum concentrations of high-sensitivity C-reactive protein (hs-CRP), tumor necrosis factor-α (TNF-α), interleukin-6 (IL-6), and interleukin-10 (IL-10), will be done at the study baseline and end of the trial. In addition, disease severity and disability will be assessed by DAS-28 and the HAQ-DI questionnaire, respectively.

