### Study design and intervention

The diagram for Standard Protocol Items: Recommendations for Interventional Trials (SPIRIT) is shown in Fig. 2. After recruiting participants, they will be stratified based on age (20 to < 40 and 40–60 years), BMI (< 30 and ≥ 30 kg/m^2^), and type of medicines (nonsteroidal anti-inflammatory drugs (NSAIDs)/disease-modifying antirheumatic drugs (DMARDs)/steroids/immunosuppressive) into different blocks and then will be randomly allocated to the intervention or control groups. For each patient in a particular block, a matched person in terms of the abovementioned variables would be placed in that block. Then, these two patients in a given block would be randomly assigned to the intervention and control groups. To do randomization, an identification code will be given to each eligible patient in each block, and then, the code of patients with the same age, BMI, and medication will be stated in the lottery container. A person who will be unaware of the study aims will be asked to draw the codes out of the container randomly. The first code will be assigned to the intervention group and the second code to the control group. This will be done for all containers. All patients, researchers, rheumatologists, statistical analysts, and laboratory staff will be blind to the intervention. Random allocation will be done by a third person who is unaware of the aim of our study. Patients in the intervention group (*n* = 20) will receive 30 g/day low-salt and low-fat probiotic cheese. Participants in the control group (*n* = 20) will receive low-salt and low-fat cheese without probiotics. Packaging of both kinds of cheeses would be in the same shape and color. The intervention will last for 12 weeks. Assessment of primary and secondary outcome variables will be done at the study baseline and end of the trial. A standard container will be given to participants, and they will be asked to that container to make sure they are consuming the specified amount. Participants will be asked not to change their lifestyle, dietary habits, and medicines throughout the study. To assess dietary intakes throughout the study, we will fill four 1-day 24-h dietary recalls (including two working days and two non-working days) once every 3 weeks by telephone interview. To complete dietary recalls, participants will be asked to report dietary intakes based on household measures. Then, we will convert the reported amounts to grams using available booklets. The average dietary intakes in these 3 days will be considered as participants’ mean dietary intakes throughout the intervention. To obtain nutrient intakes based on these food recalls, we will use the Nutritionist IV software (based on US National Nutrient Databank) modified for Iranian foods. In addition, four 1-day physical activity records (including two working days and two holidays) will be completed from all patients at weeks 3, 6, 9, and 12 of intervention to assess physical activity during the study. Participants will be requested to report all activities they have during a specific day with the name and type of activity as well as the time spent. All participants will be educated on how to record their activities throughout the study before the start of the trial. Furthermore, patients in both groups will be asked not to change their physical activity throughout the trial.

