## Study outcomes

The main primary outcome in this study would be the evaluation of serum concentrations of high-sensitivity C-reactive protein (hs-CRP). We will also consider the assessment of other inflammatory factors, including tumor necrosis factor-α (TNF-α), interleukin 6 (IL-6), and anti-inflammatory factor interleukin-10 (IL-10) as well as the assessment of disease severity and disease-related disabilities lipid profile, anthropometric measures, dietary intake, and physical activity, which all would be considered as secondary outcomes.

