### Study sample size calculation

The required sample size was calculated based on the data from a previous study [27] considering a type I error of 5% (*α* = 0.05) and type II error of 20% (*β* = 0.20, power = 80%) and hs-CRP as the key variable. We considered the mean difference in serum hs-CRP levels of 5.71 between the two groups. Also, the average SDs reported for hs-CRP in the control and intervention groups were considered as 5.93. We used the suggested formula for parallel clinical trials and reached the sample size of 17 patients in each group.
$$ n=\frac{2\times {\left({Z}_{1-\frac{\alpha }{2}}+{Z}_{1-\beta}\right)}^2\times \mathrm{SD}2}{\mathrm{d}{}^2} $$$$ n=2\times {\left(1.96+0.85\right)}^2{(5.93)}^2/{(5.71)}^2=17 $$

Based on this formula and given a 20% drop-out in each group, we will need a sample size of 20 persons for each group.

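### With outcomes measured only at baseline and week 12, LOCF is baseline carried forward: each dropout is given zero change, which biases the estimated effect on hs-CRP

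*Protocol article*

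**What the plan says.** On missing data, the Statistical analysis section states: "Missing values will be dealt with using the last observation carried forward (LOCF) method". It names no other method and no sensitivity analysis. The same section says of non-adherence that "we will use the intention-to-treat approach for data analysis". For the treatment effect it says: "To find the effect of the intervention on outcome variables, repeated measures analysis of variance (or its non-parametric equivalent) will be used". It adds that baseline differences between the groups, if there are any, will be controlled for.

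On timing, Study design and intervention states: "Assessment of primary and secondary outcome variables will be done at the study baseline and end of the trial". It also says "The intervention will last for 12 weeks". The abstract gives the same two time points for hs-CRP, TNF-α, IL-6 and IL-10. The contacts in between, described there and under Assessment of dietary intake and physical activity, collect diet and activity data only. hs-CRP is named as the main primary outcome under Study outcomes.

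On dropout, the Study sample size calculation section moves from 17 to 20 per group "given a 20% drop-out in each group".

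**The concern.** LOCF presupposes post-baseline measurements that can be carried forward, and this schedule has none. For a patient with no week-12 sample, the last observation is the one taken before she ate any of the cheese. Her change is zero by construction, and that value enters the analysis as if it had been measured.

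The primary estimate is at stake, together with every secondary outcome measured only at the two visits. A fixed share of zeros pulls a real effect toward zero. If the arms lose patients at different rates, any movement common to both arms is removed from one arm more than from the other, and that gap appears as a treatment difference. A common movement is plausible here. Entry requires a DAS-28 above 3.2 (Participants), and that score includes ESR or hs-CRP (Assessment of disease severity), so some regression to the mean can be expected.

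**Working it through.** **Inputs from the protocol article.** Between-group difference in hs-CRP Δ = 5.71 (no unit given), SD 5.93, two-sided α 0.05, power 80%, 20 randomised per arm, dropout 20% per arm. All are in Study sample size calculation.

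**Assumptions not in the documents.** 5.71 is the week-12 difference with balanced baselines. 5.93 is the SD at each visit. The baseline-to-week-12 correlation is 0.5, so the SD of change is 5.93 × √(2 × (1 − 0.5)) = 5.93. Dropout is unrelated to outcome, and hs-CRP is analysed on the raw scale.

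**1. The plan's own figure.** 2 × (1.96 + 0.85)² × 5.93² / 5.71² = 17.03, stated as 17. With unrounded normal quantiles it is 16.93, which rounds up to 17. The figure reproduces.

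**2. What LOCF does to one patient.** Imputed week-12 value = baseline, so change = baseline − baseline = 0. At 20% dropout this applies to 0.20 × 20 = 4 patients in each arm.

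**3. Expected effect with equal dropout d.** Each arm's mean change is multiplied by (1 − d), and so is the difference.

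| Dropout per arm | Expected difference (true 5.71) |
|---|---|
| 10% | 0.90 × 5.71 = 5.14 |
| 20% | 0.80 × 5.71 = 4.57 |
| 30% | 0.70 × 5.71 = 4.00 |

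With two visits, the time-by-group interaction in the repeated measures ANOVA is the between-group difference in change, so this is the quantity the planned analysis estimates. Baseline adjustment does not help, because the imputed value is the baseline itself. In simulations at 20% random dropout, the LOCF estimate averaged 4.54 to 4.6 for change-score and ANCOVA analyses alike. Observed-data estimates averaged about 5.7.

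**4. Expected effect with unequal dropout.** Let both arms fall by C, the active arm fall by a further Δ, and dropout be d_A (active) and d_C (control).

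Expected difference = (1 − d_A)(C + Δ) − (1 − d_C)C = (1 − d_A)Δ + (d_C − d_A)C

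- No true effect, 10% versus 30%, C = 3 (assumed): 0.20 × 3 = 0.6 in favour of the active arm. The simulated type I error is about 7%.
- True effect 5.71, 10% versus 30%, C = 4 (assumed): 0.90 × 5.71 + 0.20 × 4 = 5.94, an overstatement.
- The same with 30% versus 10%: 0.70 × 5.71 − 0.20 × 4 = 3.20.

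**5. Power, like for like.** The variance of change under LOCF is (1 − d)σ² + d(1 − d)m², where m is the arm's mean change. At d = 0.20 and C = 0:

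- Active arm: 0.8 × 35.16 + 0.16 × 32.60 = 33.35. Control arm: 28.13.
- Standard error: √((33.35 + 28.13)/20) = 1.753. Then 4.57/1.753 − 1.96 = 0.65, a power of about 0.74.
- Observed data, 16 per arm: 5.71/(5.93 × √(2/16)) − 1.96 = 0.76, a power of about 0.78 by the normal approximation. A t-test gives 0.75.

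Simulation with t-based tests:

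| Analysis | LOCF | Observed data |
|---|---|---|
| Change score | 0.72 to 0.73 | 0.74 to 0.75 |
| ANCOVA | 0.79 to 0.80 | 0.84 to 0.85 |

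The loss due to LOCF is therefore about 2 points for the change score and 4 to 5 points for ANCOVA. These figures assume no common change. A common change enlarges m and so makes the loss greater.

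**The case against.** The strongest case for leaving the rule alone is that it is conservative. The plan expects the same dropout in both arms, and this is a superiority trial. Under equal dropout the estimate moves toward the null. If there is also no true effect, LOCF causes no bias, and the simulated type I error stays near 5%. Under equal dropout that argument stands. It does not make 4.57 a sound estimate of 5.71, and it fails once dropout differs between arms. The 10% versus 30% split and the common fall are illustrations rather than figures from the plan, and the resulting bias of 0.6 is modest against 5.71. LOCF would also be right if patients who leave truly return to baseline, but the article gives no such rationale.

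The article allows log transformation or non-parametric tests, so the raw-scale figures may not carry over exactly. The mechanism does, because an imputed change of zero is zero on either scale.

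Three stronger readings are tempting, and the documents do not support them.

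- **Power falls from 80% to 66%.** Putting 4.57, SD 5.93 and 20 per arm into a t-test does give 66%. But the imputed zeros also shrink the variance of change, and 80% is the wrong comparator: 20% dropout leaves 16 observed per arm and 75% power with no LOCF at all.
- **LOCF gives 74% power where a proper analysis gives 85%.** That sets a change-score test under LOCF against ANCOVA on observed data, and most of the gap comes from ANCOVA's efficiency.
- **Imputed values make the standard errors too small and so inflate false positives.** Under equal dropout with no true effect, no inflation appears.

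**Conclusion.** The point holds as one about bias in the estimate. The two-visit schedule turns the only stated missing-data rule into baseline carried forward for hs-CRP and for every other outcome measured only at those visits. This is a method the article fixes, not a detail left to an unseen analysis plan. At the planned 20% dropout in each arm, unrelated to outcome, the expected effect is understated by 5.71 − 4.57 = 1.14, or 20%, whether or not baseline is adjusted for. With unequal dropout the bias can go either way and can create a difference where none exists. Its size is the dropout difference times the common change, added to the shrinkage of any true effect. The power cost is secondary: 2 to 5 points under the stated assumptions, which include a correlation of 0.5 and no common change.

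**What to change.** Replace the LOCF sentence in Statistical analysis. Any of the following would serve, each valid under missing at random:

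- a likelihood-based mixed model of the baseline and week-12 values;
- baseline-adjusted ANCOVA on observed week-12 data;
- multiple imputation with a small model using baseline outcome and arm.

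The imputation model should not be fitted separately by arm with all stratification factors. Two age, two BMI and four medication categories give up to 2 × 2 × 4 = 16 strata, against about 16 observed patients per arm. Baseline carried forward may stay as a sensitivity analysis, labelled as such.

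State also that week-12 outcomes will be sought from all randomised patients who still consent, including those who have stopped the cheese. This statement and the intention-to-treat statement must be reconciled with the post-enrolment exclusions under Participants (for example medication change or antibiotic use) and Adverse events. As written, those may add to the missing week-12 values.

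The cost is a change of wording in these sections, slightly more analysis work, and some effort to follow up patients who stop the intervention. No extra patients or scheduled visits are needed.

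### A weak normality test decides whether hs-CRP and the cytokines are analysed raw, logged or by ranks, so the primary effect measure is not fixed in advance, and the rank fallback is unnamed

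*Protocol article*

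**What the plan says.** The Study outcomes section makes serum hs-CRP the main primary outcome and lists TNF-α, IL-6 and IL-10 among the secondary ones. The Statistical analysis section applies one rule to all variables. A one-sample Kolmogorov–Smirnov (K-S) test assesses normality. Then "In the case of a non-normal distribution of a variable, we will apply the log transformation", and after that "If the variables were non-normally distributed even after log transformation, we would use non-parametric tests in the analyses". For the treatment effect, "repeated measures analysis of variance (or its non-parametric equivalent) will be used". The same paragraph says these analyses will examine intervention, time and their interaction, and will control for any group differences in baseline outcome, diet and physical activity.

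No correction for estimated mean and SD is mentioned. The rule does not say whether it applies by arm or pooled, at baseline or week 12, or to values or residuals. Under Study sample size calculation the planning is on the raw scale: "We considered the mean difference in serum hs-CRP levels of 5.71 between the two groups", with an SD of 5.93.

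**The concern.** Concentrations such as hs-CRP and cytokines are positive and commonly right-skewed, so the choice between raw and log scale matters. Here that choice rests on a test with little ability to see skewness at this sample size when its standard critical values are used. Two things are at stake. First, the target of the primary analysis (difference in means, ratio of geometric means, or rank shift) depends on the sample, and hs-CRP, TNF-α, IL-6 and IL-10 could each be reported differently. Second, if the rank branch is reached, the paragraph promises interaction and covariate control from a method it does not name, and the common candidates do not offer that control.

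**Working it through.** **Plan's own figure.** n = 2 × (1.96 + 0.85)² × 5.93² / 5.71² = 17.03, so the stated 17 per group reproduces. It is a raw-scale calculation. The standardised effect is 5.71 / 5.93 = 0.963. Recruitment is 20 per group.

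**Assumptions that are not in the documents.** No distribution is given. The check assumes a log-normal outcome with log-SD 0.75 to 1.0 and places the 0.963 SD effect on the log scale.

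**Strength of the test (simulated, no group difference, 5% level).**

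| Test | n = 20 | n = 40 |
|---|---|---|
| K-S, standard critical value, log-SD 0.75 | 8% | 31% |
| K-S, standard critical value, log-SD 1.0 | 20% | 64% |
| Lilliefors-corrected, log-SD 0.75 to 1.0 | 59–79% | 89–98% |

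For truly normal data at n = 20 the uncorrected test rejects in about 0.01% of samples, against a nominal 5%. With the assumed effect present and arms pooled (n = 40), it rejects in 42% and 76% of samples at log-SD 0.75 and 1.0.

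**Power of the rule as written (20 per group, end-of-trial values, uncorrected K-S).**

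| Analysis | log-SD 0.75 | log-SD 1.0 |
|---|---|---|
| Rule, K-S on pooled values | 80% | 81% |
| Rule, log if either arm rejects | 78% | 79% |
| Always log | 84% | 84% |
| Always raw (not the plan) | 74% | 65% |

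Loss against always log: 84 − 81 = 3 points at best and 84 − 78 = 6 at worst. Type I error of the rule is 5.0–5.1%. With a Lilliefors correction the log is chosen more often, so the loss shrinks.

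**Reach of the rank branch.** The logged values must also fail the test. With uncorrected K-S and log-normal data this happens in about 0.02% of samples or fewer. A corrected test has a true 5% level, so the branch would then be reached more often, at around that rate for pooled values.

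**What the rank branch delivers.** The Study design and intervention section has outcomes measured at baseline and end of trial only. With two time points, the time-by-group interaction is the group difference in change, so a two-sample rank test of change gives a between-group test, but without covariates. Friedman's test gives neither a between-group test nor covariate control. Rank-based ANCOVA would allow covariates, but the plan does not name it.

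**The case against.** The rule is written down in advance, runs in a fixed order, and the analysts are to be blinded. A reader might infer from a data-driven choice of test that the false-positive rate is inflated. The simulations do not support that: type I error stays near 5%.

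A reader might also take the always-raw figures (74% and 65%) as the plan's power. The plan does not prescribe an always-raw analysis. It takes logs when the test rejects, and that tends to happen in the most skewed samples. Nor is the raw scale always the likelier path: pooled at log-SD 1.0, the test rejects more often than not.

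A third tempting reading is that the fallback leaves the trial with no treatment test. That is too strong. A rank test of change is available, the section itself allows a non-parametric counterpart to the two-sample t-test, and Friedman's test is nowhere mentioned.

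Finally, a condensed article may leave the name of a fallback to a fuller document. That is fair for the name alone. It does not dispose of the main point, because the article itself states the rule that selects the scale. A mechanical rule still leaves the primary effect measure to be settled by the sample.

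**Conclusion.** The point holds as a recommended improvement, not as a threat to validity. The scale of the primary effect depends on a test that is weak at 20 per group if uncorrected, related markers may end on different scales, and the unnamed fallback in its usual forms does not give the promised covariate control.

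The cost is about 3 to 6 points of power (78–81% against 84%) under the log-normal assumptions above, and less with a Lilliefors-corrected test.

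The size depends on those assumptions. A second simulation assumed CV 0.75, 1.0 and 1.5, a true ratio of 0.6 and a baseline–end correlation of 0.5. It gives 48%, 34% and 26% for a gated test without baseline covariates, against 76%, 57% and 38% for log ANCOVA. A reader might charge that whole gap to the normality test. Part of it comes from baseline adjustment, which the plan promises where the groups differ. Against the unadjusted log time-by-group test (64%, 46%, 30%) the differences are 16, 12 and 4 points. The documents supply neither the ratio nor the correlation, so these figures show sensitivity and do not estimate the loss in this trial.

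**What to change.** Remove the K-S test as a selector of method. State that hs-CRP, TNF-α, IL-6 and IL-10 are analysed as natural logs by ANCOVA on log baseline and reported as geometric-mean ratios with 95% confidence intervals. Analyse DAS-28 and HAQ-DI on their own scales. Check model residuals, and name rank-based ANCOVA of week-12 values as a sensitivity analysis for all outcomes, so that the rank method can carry covariates.

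The cost is wording only: no extra patients, visits or assays. The downside is that the primary effect becomes a ratio, whereas the sample size rests on a raw difference of 5.71. A raw difference can be shown alongside, and the sample-size justification should be restated on the log scale.

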## Methods/design

### Participants

This study is a parallel superiority randomized clinical trial, with a 1:1 allocation ratio which will be done in 2021, in which participants will be recruited from Shariati Hospital, Tehran, Iran. Women who will meet the criteria will be included in the current study: (1) those aged 20–60 years, (2) have a body mass index (BMI) of 25–40 kg/m^2^, and (3) those who have been diagnosed with a mild to moderate RA. RA will be diagnosed by a rheumatologist using the American College of Rheumatology (ACR) criteria. Disease Activity Score-28 (DAS-28) > 3.2 will be considered as mild to moderate RA [18, 19]. Patients whose conventional medications (methotrexate, prednisolone, hydroxychloroquine, sulfasalazine) were not changed in terms of type or dosage over the past month will be included. Individuals with (1) other inflammatory diseases including pancreatitis and inflammatory bowel disease (IBD), (2) acute heart disease or kidney and liver disease, (3) gastrointestinal disorders or lactose intolerance, (4) those who are pregnant or lactating, and (5) those who were using antibiotics, pre-biotic or probiotic supplements, multi-vitamin, and mineral supplements during the last 3 months will not be included. The study would be restricted to non-smokers and non-alcoholic individuals. People who are routinely using probiotic-enriched foods in their usual diet will not be included as well. The exclusion criteria would be any alteration in the type or dosage of medicines during the intervention, taking dietary supplements or antibiotics, smoking and alcohol use throughout the study, and getting pregnant. We will also exclude patients who fasted the whole day during the study, as Muslims do during Ramadan. All participants will provide informed written consent. Moreover, the study protocol has been recorded on the IRCT website (IRCT20201120049449N1). The flow diagram of the project is shown in Fig. 1.

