## Strengths and limitations

This is the first clinical trial investigating the effects of probiotic cheese consumption on inflammatory and anti-inflammatory markers, disease severity, and symptoms in patients with RA. It should be noted that the intervention is of low cost and can easily be carried out in clinical practice. In this study, patients will be block-matched with each other in terms of several variables that might influence the findings. Several outcomes, including biochemical indicators along with subjective- and objective-based symptoms, will be examined in patients at the study baseline and end of the trial. Moreover, we will assess compliance with the intervention throughout the study. We hypothesize that probiotic cheese consumption might result in decreased inflammation and improvement in the gut microbiota, which might lead to beneficial effects on disease severity and symptoms.

The limited number of bacterial species in the probiotic cheese is the main limitation of the current project. Due to limitations in budget, we would not be able to evaluate a wide range of inflammatory and anti-inflammatory cytokines. To examine the compliance of study participants to the prescribed probiotic-containing food, one might suggest to assess trimethylamine N-oxide (TMAO); however, the lack of funding to do this would be another limitation. In addition, subjective decisions in the assessment of outcome variables might also be of concern.

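### Patients are randomised in pairs matched on age, BMI and medication, but the planned analyses include neither the pair nor these factors; the resulting error is conservative and probably small

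*Protocol article*

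**What the plan says.** **Randomisation (Study design and intervention).** Patients are stratified by two age bands, two BMI bands and "type of medicines (nonsteroidal anti-inflammatory drugs (NSAIDs)/disease-modifying antirheumatic drugs (DMARDs)/steroids/immunosuppressive) into different blocks". Each patient is joined by a matched partner, and "these two patients in a given block would be randomly assigned to the intervention and control groups". The lottery step restates the matching: "the code of patients with the same age, BMI, and medication will be stated in the lottery container". The first code drawn goes to intervention and the second to control.

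**Reason given (Strengths and limitations).** The matching is offered as an advantage: "patients will be block-matched with each other in terms of several variables that might influence the findings".

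**Analysis (Statistical analysis).** "Continuous variables will be compared between the two groups by independent samples" t-test or a non-parametric equivalent. For efficacy, a repeated measures ANOVA is planned in which "the effect of the intervention, time, and time-intervention interaction will be explored". The adjustment list is explicit: "The potential difference in baseline levels of outcome variables as well as differences in dietary intakes and physical activity levels", where the groups differ. Age group, BMI group, medication type and pair are not on it.

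**Sample size (Study sample size calculation).** The formula is the one for two independent groups, with no term for within-pair correlation.

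**The concern.** A restriction on the randomisation should be reflected in the analysis. If matched partners resemble each other on the outcome, the difference between arm means varies less from one randomisation to another than an independent-samples formula assumes. The reported standard error is then too large, the P value too large and the interval too wide.

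The article itself says that the matching variables may influence the findings, which is the condition under which this happens. With 40 patients, precision is scarce. The article also fixes the model terms and the covariates, so this is a stated choice and not a detail left to another document.

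A smaller, related point is that the medication groups are not defined so that each patient falls into exactly one. The Participants section requires that a patient's conventional medicines ("methotrexate, prednisolone, hydroxychloroquine, sulfasalazine) were not changed in terms of type or dosage over the past month") be stable, and does not make these drugs alternatives to one another. A patient taking a steroid and a DMARD fits two labels. If medication is to be a model term, it needs one value per patient.

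**Working it through.** **Inputs from the protocol article:** difference 5.71, SD 5.93, two-sided 5% level, 80% power, 20 patients per arm, outcomes measured at baseline and at end of trial.

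**Assumed, because the documents give no value:** within-pair correlation of outcome levels, ρ, from 0.1 to 0.4; correlation between a patient's baseline and end values, r, from 0.5 to 0.7; a pair effect that is the same at both visits.

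**1. The plan's own figure.** n = 2(1.96 + 0.85)² × 5.93²/5.71² = 17.03, or 16.93 with unrounded normal quantiles. The stated 17 per group reproduces, and it is an independent-groups figure.

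**2. Unadjusted t-test on end values.** The variance of the difference in arm means is 2·SD²(1 − ρ)/n, while the independent-samples formula uses 2·SD²/n. The standard error is therefore overstated by a factor of 1/√(1 − ρ). Size and power below are by simulation with 20 pairs and a standardised effect of 5.71/5.93 = 0.963.

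| ρ | SE factor | True size at nominal 5% | Power, unpaired | Power, paired |
|---|---|---|---|---|
| 0 | 1.00 | 5.0% | 84% | 82% |
| 0.1 | 1.05 | 4.0% | 85% | 86% |
| 0.2 | 1.12 | 3.0% | 87% | 90% |
| 0.4 | 1.29 | 1.4% | 90% | 96% |

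The size never exceeds 5%. Unpaired power also rises with ρ, because the balance created by matching helps even when the analysis ignores it.

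**3. The planned efficacy analysis.** With two visits, the time-by-intervention test is equivalent to a t-test on change scores. This is the test that carries the treatment effect, since the intervention main effect averages in a baseline visit at which there is none.

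- *Change score.* The covariance between partners' changes is ρ − 2ρ + ρ = 0. A stable pair effect cancels, and the size is 5.0%.
- *Adjusted for baseline.* The residual is end value − r × baseline. Its variance is 1 − r², and the covariance between partners is ρ(1 − r)². The residual within-pair correlation is ρ(1 − r)²/(1 − r²) = ρ(1 − r)/(1 + r).
  - ρ = 0.2, r = 0.7: 0.2 × 0.3/1.7 = 0.04; SE factor 1.02; simulated size about 4.6%.
  - ρ = 0.4, r = 0.5: 0.4 × 0.5/1.5 = 0.13; SE factor 1/√(1 − 0.133) = 1.07; simulated size about 3.6%.

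Under these assumptions the planned analysis has a size of about 3.6% to 5.0%, and the standard error is overstated by at most about 7%.

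**The case against.** **The t-test sentence may not describe the efficacy test.** It can be read as covering general group comparisons, with the intervention effect left to the repeated measures ANOVA. This stands as far as size is concerned: the figures in step 2 do not apply to the planned efficacy test, and those in step 3 do. It does not remove the point, because the ANOVA omits the same terms. Step 3 also assumes a stable pair effect. If the matching factors predict change itself, some correlation remains, but the documents give no sign of how much.

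**The paired analysis is not always better.** At ρ = 0 it has 82% power against 84%. This stands, and it is a reason to model the factors and not to switch to a paired t-test.

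**Stronger readings a reader might infer.**
- *That the benefit of matching is lost altogether.* Unpaired power rises from 84% to 90% as ρ goes from 0 to 0.4, so only part of the gain is forgone.
- *That drop-out would break many pairs.* The article specifies intention-to-treat with last observation carried forward, so a complete-case count of pairs does not follow from it.
- *That a patient without a match cannot be randomised.* The article says that a matched person would be placed in the block, which allows recruitment to continue until a partner is found. Any count of unmatched patients rests on assumed stratum frequencies.
- *That the overlapping medication labels make the matching unworkable.* The lottery step speaks of patients on the same medication, which can be read as the same regimen. How patients on several drugs are coded is operational detail that a condensed article may leave to the full protocol.

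**Conclusion.** The mismatch is real on the text: randomisation is within matched pairs, and no planned analysis carries the pair or the matching factors. Its direction is conservative, giving wider intervals and larger P values than the design warrants, and no inflation of the 5% error rate.

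Its size is unknown because no within-pair correlation is given. For the planned efficacy analysis it is probably small, resting on ρ up to 0.4, r of 0.5 to 0.7 and a stable pair effect. The larger loss (size down to 1.4%, power 90% against 96%) applies only to an unadjusted comparison of end values at ρ = 0.4.

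This does not threaten the trial's validity. It is a worthwhile correction because it costs little and the trial is small. The overlap of the medication labels is secondary, and matters mainly because the same variable should enter the model.

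**What to change.** In the Statistical analysis section, add age group, BMI group and medication group as fixed effects, beside the baseline value, in the primary efficacy model for hs-CRP and in the models for the other outcomes. A random pair effect is the alternative. Either keeps a patient whose partner has no end value.

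In Study design and intervention, state how a patient on more than one class of medicine is coded, so that each patient has exactly one medication group, and use that coding both for matching and in the model.

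**Cost:** one line in the model and one in the randomisation text. Two age bands, two BMI bands and four medication groups use 1 + 1 + 3 = 5 degrees of freedom, or 3 if medication has two levels. If the factors turn out not to be prognostic, there is a slight loss of power.
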